#### Interviews at 30 days, 6 and 12 months following reception into detention

6.4.3.

Young people (*N* = 80, target) who are recruited in detention will be asked if they consent to be followed up at 30 days following the interview, and again at 6 months and 12 months following the interview.

The interview that takes place at 30 days, 6 months and 12 months will be a brief ‘check-in’, principally for the purposes of gathering GEM and K-10 measures, as well as alcohol and drug questions.

#### Data linkage

6.4.4.

At the initial interview, consent will be sought from participants and their guardians to undertake data linkage to a range of records, for the purposes of understanding the profile and needs of participants, and assessing outcomes. Data sources to be linked are:

Health service usage dataAmbulance service usage dataGovernment department holding data related to young people who have experienced detention

### Analysis

6.5.

#### Quantitative analysis

6.5.1.

Quantitative data collected from Phase one will be analyzed using descriptive statistics to provide a profile of the cohort. Inferential statistics (ANOVA, Chi-squared tests, linear regression) will be used to compare sociodemographic factors and measures of mental health, and social and emotional wellbeing, and educational and criminal justice outcomes, across the three recruitment channels. Associations between sociodemographic factors and mental health and wellbeing will also be explored. Latent class analysis and/or group-based trajectory modeling will be used to analyze the trajectory of outcomes over time and to explore whether there are meaningful subgroups within the population.

GEM-Youth and K-10, along with alcohol and drug questions, collected from young people in detention (i.e., recruitment via child and youth mental health service and the Aboriginal and Torres Strait Islander unit), as well as socio-demographic data, will be used as comparison with the intervention cohort in Phase 2. Identifying data (Name, Date of Birth, Address) will be used for the purposes of data linkage.

The GEM-Youth will be piloted during the first five interviews of this study. Any issues identified with language, understanding or logistics of this tool will be discussed among investigators [name], [name], [name] and [name], and a decision will be made as to whether modifications to the tool are required. Following completion of initial interviews, the GEM-Youth will be validated, against the K-10. The methodology will follow the approach taken by Haswell et al. (26), in their Psychometric validation of the GEM. The psychometric properties and internal structure of the GEM (Adult) was examined against the K6 and K6 + 2, utilizing Pearson’s correlations, Cronbach’s alpha, and Principal Components Analysis.

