#### Aboriginal and Torres Strait Islander young people with experience of detention

6.4.1.

The target sample size for Phase one recruitment is 110 individuals, comprising 80 individuals who are received into detention within the last 7 days, during the recruitment period, and 30 individuals who are in the community, but had an experience of youth detention in the 12 months prior or who are in detention, but have been in detention for more than 7 days during the period of data collection. Individuals will be recruited over an approximate 8-month period commencing in July, 2021.

All young people who agree to participate in Phase one of this research will be invited to participate in an initial interview. The 80 individuals who are recruited within 7 days of detention will also be invited to participate in a series of follow-up interviews that will provide baseline data for quantitative comparison. Planned follow up interviews will take place at 30 days following the initial interview, 6 months following the initial interview and 12 months following the interview. Interview schedules are described below.

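### Latent class and group-based trajectory models, as the stated analysis of outcomes over time, will usually split a homogeneous cohort into groups if repeated scores correlate at about 0.3 or more

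*Protocol article*

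**What the plan says.** The quantitative analysis section (6.5.1) names ANOVA, chi-squared tests and linear regression for comparing the three recruitment channels, and also plans to explore associations between sociodemographic factors and wellbeing. For change over time it says that "Latent class analysis and/or group-based trajectory modeling will be used to analyze the trajectory of outcomes over time", with the second purpose "to explore whether there are meaningful subgroups within the population".

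The repeated interview data come from one part of the sample. Section 6.4.1 states that "The target sample size for Phase one recruitment is 110 individuals", of whom "80 individuals who are received into detention within the last 7 days" are to be followed up. The other 30 have an initial interview only. On timing, "Planned follow up interviews will take place at 30 days following the initial interview, 6 months following the initial interview and 12 months" after it, which gives four time points with the initial interview. Section 6.4.3 describes the later interviews as "principally for the purposes of gathering GEM and K-10 measures, as well as alcohol and drug questions".

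The article also plans data linkage "for the purposes of understanding the profile and needs of participants, and assessing outcomes" (section 6.4.4). It gives no ICC, no expected loss to follow-up, no rule for the number of classes and no within-class covariance structure.

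**The concern.** Standard group-based trajectory modelling treats a person's repeated scores as independent once the class is known. Latent class analysis of the repeated measures makes the same assumption. If young people simply differ in their usual level of distress or wellbeing, their scores correlate across visits, and these models can reproduce that correlation only by adding classes. A criterion such as BIC that compares one, two or three such classes does not reveal the problem, because every candidate shares the assumption.

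Two things are at stake. Phase one findings inform the provisional service model, and the quantitative findings will be published (section 8), so artificial groups could be read as real subgroups of need. The GEM-Youth and K-10 data of this cohort are also the Phase 2 comparator (sections 6.4.1 and 6.5.1), for which the average course with its uncertainty is the natural summary. The methods named for trajectories do not target that directly.

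**Working it through.** **The plan's own figure.** The only figure that can be checked is the sample size: 80 + 30 = 110, which is correct. The article states no error rate for finding subgroups.

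**Inputs from the article.** N = 80 (a target) with interviews at months 0, 1, 6 and 12.

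**Assumed inputs.** ICC from 0 to 0.7; the number of groups chosen by lowest BIC; no loss, or 40% lost by 12 months.

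**Data simulated.** One population without subgroups and with a flat mean: y_it = √ICC · b_i + √(1 − ICC) · e_it, with b and e standard normal.

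**Model fitted.** Within class k, y_it = α_k + β_k t + error, with a common residual variance and no within-class random effect. Parameters: p = 2K + 1 + (K − 1), so 3, 6 and 9 for K = 1, 2 and 3. Selection maximises log L − ½ p ln N.

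**Why it fails, by hand.** Each extra class costs 3 × ½ ln 80 = 1.5 × 4.382 = 6.57 log-likelihood units. The expected gain from describing the correlation fully, over a one-class independence model, is −(N/2) ln[(1 + 3ρ)(1 − ρ)³], with ρ the ICC. At N = 80:

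- ρ = 0.1: −40 × ln(0.9477) = 2.15, below 6.57
- ρ = 0.2: −40 × ln(0.8192) = 7.98, a little above
- ρ = 0.3: −40 × ln(0.6517) = 17.13, far above

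A grouped model captures only part of this gain, so these figures are a guide to where the rate climbs; the rates themselves come from simulation. At N = 300 and ρ = 0.1 the gain is −150 × ln(0.9477) = 8.06 against a penalty of 1.5 × ln 300 = 8.56. The gain grows with N and the penalty only with ln N, which is why a larger sample does not help.

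**Simulated share choosing two or more groups** (120 data sets per cell, K = 1 to 3, linear unless stated):

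| ICC | N = 80, complete | N = 80, 40% lost | N = 80, quadratic | N = 300, complete |
|---|---|---|---|---|
| 0 | 1% | 0% | 2% | 1% |
| 0.1 | 16% | – | – | 51% |
| 0.2 | 78% | – | – | – |
| 0.3 | 97% | 85% | 96% | 100% |
| 0.5 | 100% | 100% | 100% | 100% |
| 0.7 | 100% | 100% | 100% | – |

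The Monte Carlo standard error is at most √(0.5 × 0.5/120) = 4.6 points. Repeat runs with other seeds and fitting settings gave 11-18% at ICC 0.1, 71-78% at 0.2, 96-100% at 0.3 and 100% at 0.5 and 0.7 for complete data. Requiring every class to hold at least 5% of participants with a mean posterior probability of at least 0.70 changed almost nothing (97% at ICC 0.3, 100% at 0.5).

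**Latent class version.** With continuous scores and a free mean at each visit (latent profiles), the rates were 91%, 100% and 100% at ICC 0.3, 0.5 and 0.7. Binary alcohol and drug items were not simulated.

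**Effect of the proposed check.** Requiring the grouped model also to beat a one-class random-intercept model on BIC cut false subgroups to 0-5% across runs with normal heterogeneity. With skewed (gamma) heterogeneity the remaining rate for trajectory models was 2-19% across runs at mild to moderate skew. At strong skew (skewness 2) it was 39%, 48% and 41% at ICC 0.3, 0.5 and 0.7.

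**The case against.** **The failing inputs are not in the article.** It names no ICC and no selection rule, and a condensed article may leave class enumeration and covariance structure to an analysis plan. This stands, so the size of the problem is conditional. If BIC counts 320 observations (80 × 4) instead of 80 persons, the rates fall to 4% at ICC 0.1 and 46% at 0.2, but stay at 96-100% from 0.3 up. The choice of model family, however, is made in the article.

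**Neither named method is fixed, and a variant could escape.** A growth mixture model with a within-class random intercept found false classes in only 0.5-1.5% of data sets under normal heterogeneity. The article does not name that model, and under skewed heterogeneity it found them in 19%, 42% and 66% at ICC 0.3, 0.5 and 0.7.

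**The subgroup aim is already exploratory.** True, and choosing two groups by BIC is not yet calling them meaningful. But the same sentence also gives the class models the plain task of analysing the course over time.

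**Stronger readings that a reader might infer.** One is that 80 people and four visits are too few. The simulations contradict this: the false rate rises at N = 300, and linked outcomes could draw on up to 110 people. A second is that the average course will never be estimated. A Phase one article cannot show that, since the comparison belongs to a Phase 2 plan not at hand. A third is that false classes would steer the service design. Sections 6.1 and 6.2 build the model through consultation and a consensus workshop, and nothing ties it to trajectory classes.

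**Conclusion.** The concern holds in conditional form. For repeated GEM-Youth and K-10 scores, the two named methods in their standard forms, with classes chosen by BIC, will usually return two or more groups from a cohort that has none if the ICC is about 0.3 or more. The size for trajectory models with complete data is 97-100% at that level, 71-78% at 0.2, 11-18% at 0.1 and about 1% at 0. At ICC 0.3 it falls to 85-90% with 40% lost by 12 months. That distress and wellbeing scores correlate at 0.3 or more within a person is an assumption, though a reasonable one to plan for. The fault lies in the absence of within-class variation, not in the number of participants or visits.

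**What to change.** In section 6.5.1, separate the two purposes.

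- **Average course.** Describe GEM-Youth and K-10 in the followed-up cohort with a linear mixed model (participant random intercept, visit as a factor), and report visit means with 95% confidence intervals.
- **Subgroups.** Keep latent class and trajectory models for the exploratory question. Call subgroups meaningful only if the class model also beats a one-class random-effects model on BIC.
- **Limit of the check.** State that it greatly reduces false subgroups but does not eliminate them when scores are skewed.

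The cost is a little more analysis and a few sentences of text, with no change to recruitment or data collection. The downside is that Phase one will probably support fewer subgroup claims, or none.

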#### Qualitative analysis

6.5.2.

Interviews will be audio-recorded and stored in a re-identifiable form and be partially transcribed by project team members. Drawings produced during the initial interview will be copied with permission of the young person and the original returned if they wish.

Qualitative data will be analyzed using an inductive thematic approach, structured within the framework of the *Ngaa-Bi-Nya* landscape prompts (35). Analysis will include ongoing consultation with the Cultural Governance Group throughout, to ensure that culturally specific meanings and nuances are not missed and that findings are presented in a culturally safe way. Data presented in publications will be assigned a pseudonym, with no identifying details accompanying excerpts or artworks that may appear in publication.

## Remuneration

7.

Participants will be remunerated for their time with a $20 voucher (e.g., Rebel Sport, Kmart, Cotton On or City Beach) (initial, 30 days, and 6 months), except for the last payment (12 months), where they will receive $30. Participants who complete data collection at one time point over two sessions, will receive their payment on completion of all data collection activities for that time point. In line with Aboriginal and Torres Strait Islander ways of doing, remuneration processes align with the principle of reciprocity when sharing personal stories. Given the relatively low risks of participation in this study, and processes we have in place for managing wellbeing risks, we believe that remuneration is both ethically and culturally important (36).

Participants will also be offered the opportunity of submitting something to appear on the project website^1^ e.g., a story, artwork, recipe or joke. These contributions will be anonymous and an opportunity, only if the young person is interested.

### Other stakeholders (≥18 years)

7.1.

As above, individual level data will not be collected from other stakeholders in Phase one for the purposes of research, and these participants will not be remunerated. However, where possible reciprocity will be shown through provision of opportunities for training or refreshments being provided at events. If members of the community are asked to facilitate any engagement activities (e.g., as a Chair), they will be remunerated for their time in line with relevant university policies.

## Publication and dissemination

8.

Findings from Phase one will be used to inform the development of a provisional model of service for a social and emotional wellbeing intervention that will be implemented in Phase two. Additionally, quantitative findings will be published in reports, academic articles and conference presentations. Findings from interviews undertaken with young people will be produced into a booklet, comprising narratives and artwork, that can be gifted back to project participants and distributed among other project stakeholders as well as be used in publications.

## Cultural and ethical considerations

9.

### Cultural integrity

9.1.

To ensure cultural integrity of the project, process and outcomes, Aboriginal and Torres Strait Islander ways of being, knowing and doing have been embedded into all aspects of the research processing including the co-design. Application of Aboriginal and Torres Strait Islander principles and practices govern processes including integrity, inclusivity, respect, reciprocity, participative, outcomes focused and promotes self-determination to challenge system barriers including systemic racism. Cultural integrity includes holistic considerations of the individual young person, family and community, and kinship structures, as well as protocols for service design.

As identified earlier, the governance structure and roles of the Aboriginal and Torres Strait Islander Cultural Governance Group works with and provides input into all project activities with the other project groups [Chief Investigator Group (CIG), Evaluation Working Group (EWG), Operations Working Group (OWG)], broadly, and specifically with respect to the values of spirit and integrity, cultural continuity, equity, reciprocity, respect, and responsibility.

A key role is to ensure that the work reflects and acknowledges the broader policy and research context regarding development of mental health and social and emotional wellbeing services including, but not limited to:

The Cultural Respect Framework for Aboriginal and Torres Strait Islander Health (37)A National Strategic Framework for Aboriginal and Torres Strait Islander Peoples’ Mental Health and Social and Emotional Wellbeing (6)Values and Ethics: Guidelines for Ethical Conduct in Aboriginal and Torres Strait Islander Health Research (36)

This includes monitoring and providing feedback to the CIG, OWG and EWG on these matters, specifically to monitor and identify cultural risks and measures including development of data sovereignty to ensure culturally safe data collection, analysis and presentation. The data is considered through a cultural community lens to ensure that all data is not mis-interpreted or mis-represented.

### Risks

9.2.

#### Risks of disempowerment or discomfort

9.2.1.

Research in correctional settings can be an empowering experience for participants in spite of limitations because of the location, context and perception of research being invasive. The data collection strategy for this project has been developed in consultation with Aboriginal and Torres Strait Islander investigators and stakeholders, to ensure that it is trauma-informed and empowering. Use of the GEM will ensure that the interview follows a strengths-based approach. A supportive interview context within which to manage risks will be actively constructed for IMHIP-Youth, managed in a variety of ways including:

Ensuring the research is explained and recruitment is undertaken by an Aboriginal or Torres Strait Islander staff member or staff member experienced in engaging well with young people,Provision of training to all staff who will support recruitment, including training in study design and purpose, cultural protocols for engagement and obtaining consent,Inclusion of parents or community guardians in consenting process, including in-custody, andProvision of age and culturally appropriate written project materials, as well as explanation of the study

#### Consent risks

9.2.2.

Several mechanisms are in place to ensure that young people have capacity to provide informed consent and that their parents and guardians, both in-custody and community, are engaged and have the opportunity to provide their consent to the young person’s participation. These measures are as follows:

Eligibility to participate based on capacity to consent will be assessed by child and youth mental health service clinician or a youth detention Aboriginal and/Torres Strait Islander staff member, to ensure that the young person has sufficient understanding, intelligence and maturity to appreciate the nature, consequences and risks of consenting to participate in the study and the alternatives, including the consequences of not consenting to participate.Young people will be provided with both written project documents, that are culturally and age appropriate, as well as having the project and the nature of their participation explained to them verbally.Parents and/or guardians will be engaged in the consenting process, irrespective of whether the young person is being engaged in-custody or community.

#### Risks due to sensitive questions

9.2.3.

Young people who experience detention are more likely than young people in the community to have experienced traumatic life experiences that may be recounted in the process of a narrative interview. Consequently, there is a risk that engagement could cause distress to participants. To manage any risk of harm, interviewers will undergo thorough training in cultural protocols and interviewing techniques as well as trauma informed care. Interviewers will also be provided supervision by a senior clinician. Done well, participating in a narrative interview with a trained interviewer who engages in deep-listening, may be therapeutic and in this project, the interview will follow the completion of the GEM, a trauma-informed strengths based tool. A senior child and youth forensic mental health psychiatrist will be on-call for the duration of the project, to provide advice where a researcher or clinician raises concerns about acute mental health deterioration or a participant’s safety, and to facilitate an appropriate care response. Any emergent distress or concerning statements (e.g., disclosures of suicidality) will be taken seriously, and the researcher will contact relevant Youth Justice staff and the senior child and youth mental health psychiatrist, or his appointed delegate, to seek advice, undertake safety planning, and ensure that appropriate follow-up is provided. If such an event occurs, a review will take place through the Operational Working Group, to identify any issues or learnings relating to the conduct of this research.

#### COVID-19 risks

9.2.4.

The COVID-19 pandemic is having unforeseen and unforeseeable impacts on daily activities, globally. It is likely that COVID-19 will impact upon this project, in terms of its impacts on social and emotional wellbeing, delays due to periodic restrictions on face-to-face meetings, potential impacts on comparator data collection, and rapid shifts in the services landscape. Impacts are already being addressed through the addition of retrospective time points, to assist in disentangling impacts of COVID versus the proposed intervention on social and emotional wellbeing. If required, the project team will substitute the planned face-to-face stakeholder workshop with an online forum, and if/when face-to-face recruitment is not possible, the project team will undertake video-link engagement participants.

#### Staff risks

9.2.5.

Some research staff will be involved in face-to-face data collection that they may find distressing. Some staff will be required to travel offsite for data collection. Any distress will be managed through debriefs with supervisors, with services readily available through The University of Queensland, if required. Risks related to offsite work will be minimized by ensuring that staff do not travel alone. Offsite data collection will be arranged in suitable locations that ensure researcher safety (e.g., rooms in local health services).
